#### Recruitment and sample size

2.2.1

This study plans to use a consecutive enrollment strategy between February 2026 and December 2026. Specialized personnel from the hospital Information Department (not involved in this study) will conduct an initial screening of anonymized data from the electronic health record system to identify patients who meet the diagnostic criteria for multimorbidity. Subsequently, research assistants will independently review the data in pairs based on predetermined inclusion and exclusion criteria. Once eligibility is confirmed, independent recruitment staff will contact potential participants using compliant contact information recorded in the hospital system and invite them to join the study after obtaining informed consent.

The sample size calculation is based on the primary outcome (systolic blood pressure). According to previous similar research (34–36), the optimistic but clinically significant effect size hypothesis was adopted. The expected systolic blood pressure after 3 months of intervention is set as follows: 138.2 mmHg for the routine health education group, 132.0 mmHg for the universal AI group, and 127.0 mmHg for the TCM-constitution–based AI group. The common inter-group standard deviation (*σ*) is set at 16.3 mmHg. Using G*Power 3.1 software with one-way ANOVA (F tests), two-sided *α* = 0.05, and power (1 − *β*) = 90%, the required sample size is 55 participants per group, totaling 165 participants. Considering an estimated 20% dropout rate, the final planned recruitment is 207 participants, or 69 per group. If the true intervention effect size is smaller than the assumed, the statistical power of this study will be correspondingly reduced, and the results should be interpreted with caution and regarded as preliminary exploratory evidence.

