#### Primary outcome

2.5.1

Change in systolic blood pressure from baseline to month 3 (T1). Systolic blood pressure (SBP) is selected due to its continuous, independent, and direct positive association with cardiovascular risk (2), and strong evidence that effective SBP control reduces cardiovascular events and all-cause mortality (38).

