#### Key secondary outcomes

2.5.2

Physiological indicators: HbA1c, blood fat, BMI, diastolic pressure.Self-management behavior modification: ability to self-manage chronic disease, medication adherence, physical activity, level of engagement, Self-Regulation of Eating Behavior.Quality of life and psychological indicators: quality of life, anxiety, depression, self-efficacy, Perceived Social Support.

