### Statistical analysis

2.7

Statistical analyses will be performed using SPSS 26.0 (or R). Continuous variables with normal distribution will be presented as mean ± standard deviation; non-normally distributed variables as median (interquartile range).

All primary and key secondary analyses will adhere to the intention-to-treat principle. To evaluate the effect of the intervention on health outcomes, under the assumption of data missing at random, a linear mixed-effects model will be applied. Time, group, and their interaction will be included as fixed effects, and a random intercept will be added for each participant to control for baseline heterogeneity. Baseline values and age will be included as covariates.

Between-group differences at each time point will be estimated using the EMMEANS package to compute estimated marginal means (EMMs), followed by adjusted pairwise comparisons (e.g., Tukey multiple comparison tests). To assess overall changes from baseline to the end of follow-up, model-estimated baseline-adjusted marginal means at the endpoint will be compared among the three groups. The family-wise error rate for primary and key secondary outcomes will be controlled using the Bonferroni method. A *p*-value < 0.05 will be considered statistically significant.

Sensitivity analyses will be conducted to assess the robustness of the findings:

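### Holm's step-down would give the same 5% family-wise control as the planned single-step Bonferroni and never reject less: a cheap improvement, usually of modest size, not an error

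*Protocol article*

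**What the plan says.** Section 2.7 (Statistical analysis) names one multiplicity procedure across outcomes: "The family-wise error rate for primary and key secondary outcomes will be controlled using the Bonferroni method". It gives no step-down, ordering or split of alpha, and no reason for choosing the single-step form. The next sentence sets the threshold: "A *p*-value < 0.05 will be considered statistically significant". Within an outcome, the three arms are compared at each time point from estimated marginal means, "followed by adjusted pairwise comparisons (e.g., Tukey multiple comparison tests").

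Section 2.5.2 lists the key secondary outcomes in three groups:

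- "Physiological indicators: HbA1c, blood fat, BMI, diastolic pressure" (4 items);
- "ability to self-manage chronic disease, medication adherence, physical activity, level of engagement, Self-Regulation of Eating Behavior" (5 items);
- "quality of life, anxiety, depression, self-efficacy, Perceived Social Support" (5 items).

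That makes 14. With the primary outcome of section 2.5.1, the change in SBP to month 3, the family has 15 outcomes as listed.

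**The concern.** Bonferroni applies its strictest threshold to every test, however many hypotheses have already been rejected. Holm applies that threshold only to the smallest p-value and relaxes after each rejection. Both rest on the same inequality and need no assumption about the correlation between outcomes. Bonferroni can therefore lose rejections relative to Holm and can never gain one.

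The second aim, on self-management behaviour, rests entirely on key secondary outcomes, as do the metabolic, quality-of-life and psychological results. A lifestyle programme may well move several related outcomes together, and that is where a step-down rule gains most. Section 2.2.1 itself describes the assumed SBP effect as optimistic and accepts that power will fall if the truth is smaller, so power that costs no error protection is worth having.

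**Working it through.** **1. The plan's own figure.** Section 2.2.1 gives month-3 SBP means of 138.2, 132.0 and 127.0 mmHg, SD 16.3, and "two-sided *α* = 0.05, and power (1 − *β*) = 90"%. Cohen's f is the SD of the three means divided by 16.3, which is 0.281. One-way ANOVA power is 0.898 at 54 per group and 0.903 at 55, so 55 per group (165) reproduces. For dropout, 55/0.8 = 68.75, which rounds up to 69 per group and 207 in all.

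**2. Thresholds.** With m p-values in the family:

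- Bonferroni compares every p-value with 0.05/m. For m = 15 this is 0.0033; for m = 14 it is 0.0036.
- Holm compares the j-th smallest with 0.05/(m − j + 1) and stops at the first failure. For m = 15 it starts at 0.05/15 = 0.0033, reaches 0.05/10 = 0.005 after five rejections, and ends at 0.05.

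Holm's thresholds are never below Bonferroni's, so every Bonferroni rejection is also a Holm rejection. The first threshold is the same for both, so the chance of rejecting at least one hypothesis is identical.

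**3. Error rate.** In simulations with correlations of 0, 0.3 and 0.5, Holm's family-wise error stayed at or below 0.05. The largest value for 14 outcomes was 0.0489, with no true effects and correlation 0, where Bonferroni gave the same. With 7 of 14 outcomes affected it was 2.7% to 3.8%, against 2.1% to 2.5% for Bonferroni. Holm missed no Bonferroni rejection.

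**4. Size of the gain.** The article gives no effect sizes for the secondary outcomes. As a range, the plan's three SBP contrasts were used, with 0.50 added as an intermediate value:

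- TCM-adapted versus universal: (132.0 − 127.0)/16.3 = 0.31
- universal versus control: (138.2 − 132.0)/16.3 = 0.38
- TCM-adapted versus control: (138.2 − 127.0)/16.3 = 0.69

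The Bonferroni power per test can be checked by hand. At d = 0.69 with 55 per arm the mean of z is 0.687 × √(55/2) = 3.60. The two-sided critical value at 0.0036 is 2.91. Power is Φ(3.60 − 2.91) = Φ(0.69), about 0.755.

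Average power per truly affected outcome for 14 outcomes, one contrast, 55 per arm, assumed correlation 0.3:

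| d | Bonferroni | Holm, 5 affected | Holm, 8 affected | Holm, all 14 affected |
|---|---|---|---|---|
| 0.31 | 9.6% | 9.9% | 10.3% | 10.9% |
| 0.38 | about 18% | 18.6% | 19.0% | 21.2% |
| 0.50 | about 39% | 40% | 42% | 47% |
| 0.69 | 76% | 78% | 80% | 88% |

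With 5 to 8 outcomes affected, the gain is 0.3 to about 3 points for d from 0.31 to 0.50 (9.9 − 9.6 = 0.3; 42 − 39 = 3) and 2 to 4 points at d = 0.69. With all 14 affected it reaches 88 − 76 = 12 points at d = 0.69.

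Using 15 outcomes instead of 14 changes little. With every outcome affected and 80% unadjusted power per test, average power rises from 45–46% to 55–56% for 14 outcomes and from 45% to 54–55% for 15.

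**5. The family must stay whole.** The plan puts SBP and the key secondaries in one family. If SBP kept 0.05/15 while Holm ran at 0.05 on the 14 secondaries alone, the bound on the family-wise rate would be 0.05/15 + 0.05 = 0.0533, above 5%.

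**The case against.** The strongest reply is that nothing here is wrong. Bonferroni is valid and pre-specified, it meets the stated aim of family-wise control, and it gives simple simultaneous intervals that agree with its decisions. That suits an analysis built on estimated marginal means. All of this stands, and preferring that agreement to a small power gain is a legitimate choice. The article does not give it as a reason, however, and Bonferroni-adjusted intervals can still be shown beside Holm p-values.

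A second reply is that the gain is small in likely settings. This also stands. A reader might infer a large loss from the chance of detecting every true effect, which rises from about 16% to 59% in the most favourable setting. That needs all 14 outcomes to be affected at 0.69, the largest of the plan's contrasts. With 5 affected at that size the rise is from 37% to 42%.

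Third, the count of 14 is soft. Blood fat may mean several lipids. Engagement, if it means platform use, cannot be compared with a control arm that has no access to the platform. The article also does not say whether contrasts and time points enter the count, which may be left to the analysis plan. These points change the size of the gain. Holm's ordering over Bonferroni holds for any m.

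Fourth, a reader might infer that Holm can be applied to the secondaries alone at the full 5% with SBP tested beside it. The article does not support that: it defines one family, and the bound would be 5.33%.

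**Conclusion.** The point holds as a cheap improvement, not as an error. Section 2.7 fixes a single-step rule where a step-down rule gives the same 5% control under any correlation and never rejects less. The direction is certain. The size rests on assumed secondary effects, an assumed correlation of 0.3, one contrast and 55 per arm. On those terms the typical gain is between a fraction of a point and about 4 points of average power per true effect. The gain of about 12 points applies only if every outcome responds at 0.69.

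A reader might also infer that Holm repairs the position of the primary outcome. It does not. Within a family of 15 outcomes, SBP would still have to pass 0.0033 if it gave the smallest p-value, and Holm does not secure it a test at 0.05. Whether SBP belongs in the family is a separate question.

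**What to change.** In section 2.7, replace the Bonferroni method with the Holm step-down procedure, applied to the same whole family (primary and key secondary outcomes) and to the same p-values that Bonferroni would have used, and report Holm-adjusted p-values. State which p-values form the list, because Holm depends on their order: one per outcome gives 15, and three arm contrasts per outcome at one time point give 15 × 3 = 45. If Tukey is kept within outcomes, an outcome should release its share of alpha only after all its contrasts have been rejected.

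If SBP is instead taken out of the family, run Holm on the key secondaries only, at the alpha left for them, so that the total stays at 5%. For example, if SBP keeps 0.05/15 = 0.0033, the secondaries have 0.05 − 0.0033 = 0.0467.

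The cost is a short change of wording, made before unblinding, and a standard option in R, which the plan allows. The drawback is that no simple simultaneous intervals match Holm decisions. Bonferroni-adjusted or unadjusted intervals would be reported alongside and labelled as such.

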To evaluate the effectiveness of the AI-HEALS system—particularly its TCM-adapted version—compared with routine management and generalized mobile health interventions in improving clinical outcomes among patients with chronic disease multimorbidity.To assess the effectiveness of the system in enhancing chronic-disease self-management behaviors.

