#### Blinding

2.3.2

This study adopts a single-blind design. Due to the nature of the interventions, participants and intervention providers cannot be blinded. However, research assistants responsible for collecting outcome data and statisticians conducting the final data analysis will remain blinded to group allocation. Research assistants will not know participants’ group assignments during clinical measurement and questionnaire collection. Statisticians will analyze de-identified datasets and will not access files containing allocation information before the analysis is completed.

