Adherence analyses: To examine the impact of intervention adherence, a per-protocol analysis will be performed. Participants meeting the pre-defined criterion for high adherence will be included, and results will be compared with the primary intention-to-treat analysis.Missing Date: To evaluate the robustness of findings against departures from the missing-at-random assumption, a worst-case scenario analysis will be performed. In this analysis, missing values in the intervention groups will be imputed under the assumption of clinical deterioration, whereas missing values in the control group will be imputed under the assumption of improvement.Exploratory analyses will be conducted to generate hypotheses for future research. These will include:Subgroup analyses: Treatment effect heterogeneity will be explored across subgroups defined by baseline characteristics (e.g., age, sex, having all three conditions) by adding relevant interaction terms to the linear mixed-effects model.Analysis by Comorbidity Pattern: This analysis will specifically examine whether intervention effects differ among participants with varying multimorbidity patterns (e.g., hypertension + diabetes vs. Hypertension +hyperlipidemia vs. all three conditions).

Results from all Exploratory Analysis will be interpreted with caution due to reduced statistical power. For exploratory outcomes (TCM constitution type transformation), the focus will be on estimating effect sizes and confidence intervals rather than hypothesis testing. When multiple *p*-values need to be combined, Stouffer’s Z-score method will be utilized.

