### Data security

3.3

Data will be double-entered and cross-checked by two independent staff members. Electronic data will be stored on password-protected encrypted servers with strictly restricted access. Unblinding will occur only after study completion and final data analysis, under supervision from the DMC and conducted only by the principal investigator and statistician.

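### The worst-case missing-data rule imputes both app arms as deteriorated, so it is not a worst case for the TCM-adapted versus universal comparison

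*Protocol article*

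**What the plan says.** The missing-data sensitivity analysis in the protocol article (2.7, Statistical analysis) has a general purpose: "To evaluate the robustness of findings against departures from the missing-at-random assumption, a worst-case scenario analysis will be performed". The rule is then fixed by arm. For the app arms it reads: "missing values in the intervention groups will be imputed under the assumption of clinical deterioration". Under 2.1 (Study design), the intervention groups are UG and TG. For the remaining arm, CG, the direction is reversed: "missing values in the control group will be imputed under the assumption of improvement".

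The comparison between UG and TG matters to the trial. The first aim, at the end of the Background, is to evaluate the system, "particularly its TCM-adapted version—compared with routine management and generalized mobile health interventions". Section 2.7 plans multiplicity-adjusted pairwise comparisons among the three groups at each time point. The limitations paragraph of the Discussion says that only the logic generating the content is meant to differ between groups.

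On blinding, 2.3.2 says that the statisticians "will not access files containing allocation information before the analysis is completed". Section 3.3 (Data security) adds: "Unblinding will occur only after study completion and final data analysis".

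**The concern.** A worst-case imputation tests a claim by setting the missing values against it. For a claim that TG lowers systolic pressure more than UG, the adverse setting is poor values in TG and good values in UG. The stated rule gives both arms poor values, so the penalties cancel wholly or in part. If UG has more dropout than TG, the net effect helps TG.

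At stake is what the trial can say about the robustness of its TCM-content finding. The analysis is described as covering the findings in general, so a reader could take an unchanged TG−UG result as having passed a severe test when it had not been put to one.

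The second, smaller matter is that the rule is arm-directed, whereas 2.3.2 and 3.3 keep allocation closed until the analysis is finished. The three passages do not say how the imputation is to be done within that restriction.

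**Working it through.** **Inputs from section 2.2.1.** Expected month-3 systolic pressure is 138.2 (CG), 132.0 (UG) and 127.0 (TG) mmHg. The SD is 16.3 mmHg, with 55 per group before dropout, 20% dropout and 69 per group recruited.

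**The plan's own figure.** The mean of the three means is 132.4, and the squared deviations are 33.64, 0.16 and 29.16. Then f = √(62.96/3)/16.3 = 0.281. The one-way ANOVA F test at α = 0.05 has power 0.898 at 54 per group and 0.903 at 55. Dropout inflation gives 55/0.8 = 68.75, so 69, and 165/0.8 = 206.25, so 207. The sample size reproduces and is not in question.

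**Assumptions for the imputation check.** The article gives no imputed value, so D is assumed at 5, 10 or 16.3 mmHg (the last is one SD). The arithmetic is on arm means, not on the fitted mixed model. Let d be the share missing in an arm. Negative differences favour the first-named arm.

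**Reading A: missing values shifted by D from the arm mean.**
- TG mean = 127.0 + d_TG·D
- UG mean = 132.0 + d_UG·D
- CG mean = 138.2 − d_CG·D
- Hence TG−UG = −5.0 + D·(d_TG − d_UG)

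Results under the planned rule (mmHg):

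| Missing TG / UG / CG | Contrast | D = 5 | D = 10 | D = 16.3 |
|---|---|---|---|---|
| 20 / 20 / 20% | TG−CG (planned −11.2) | −9.2 | −7.2 | −4.7 |
| 20 / 20 / 20% | UG−CG (planned −6.2) | −4.2 | −2.2 | +0.3 |
| 20 / 20 / 20% | TG−UG (planned −5.0) | −5.0 | −5.0 | −5.0 |
| 15 / 25 / 20% | TG−UG | −5.5 | −6.0 | −6.6 |
| 25 / 15 / 20% | TG−UG | −4.5 | −4.0 | −3.4 |

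The contrasts with control are stressed as intended. TG−UG is untouched at equal dropout, moves in TG's favour when UG loses more, and is stressed only in part when TG loses more.

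**Reading B: one common poor value W for every missing app-arm participant.** With equal d, TG−UG = (1 − d)(127.0 − 132.0). At d = 0.20 this is 0.8 × (−5.0) = −4.0 for any W.

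**A worst case for TG against UG.** With TG deteriorated and UG improved, TG−UG = −5.0 + D·(d_TG + d_UG). At 20% missing in each arm:
- D = 5: −5.0 + 2.0 = −3.0
- D = 10: −5.0 + 4.0 = −1.0
- D = 16.3: −5.0 + 6.52 = +1.5

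**Blinding.** The planned rule needs one fact about the coded arms, namely which is control. Nothing in 2.3.2 or 3.3 provides for that before the analysis is completed, and 2.7 does not say that this analysis follows unblinding.

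**The case against.** Several limits on this point stand.

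- **TG−UG need not stay fixed.** A zero shift depends on moving values from the arm mean. Clinical deterioration could equally mean one common poor value, in which case TG−UG falls by 1.0 mmHg. That is dilution by the missing share and still short of a worst case, but it is not zero.
- **The sizes scale with D.** The article fixes no D, so no single figure, or percentage of effect erased, should be quoted as the size of the flaw. That the rule does not set the two app arms against each other is independent of D.
- **The SAP is not shown.** Imputed values, further scenarios and the person who imputes may be set out there, so their absence here is no fault. The point concerns only the direction that the article does fix.

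A reader might also infer that the rule will overturn real effects against control, or that a tipping-point analysis is obligatory. The documents support neither. On the assumptions above, UG−CG changes sign only at D = 16.3 and TG−CG at none of the three values. No significance calculation was made. A bounding analysis is meant to be severe, nothing in 2.7 lets it override the primary model, and for the contrasts with control the choice between bounding and tipping-point analysis is a matter of preference.

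Finally, a reader might infer that a blinded statistician cannot run the rule. That is too strong. With coded arms it can be run under each of the three possible control labels and the right run picked out at unblinding.

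**Conclusion.** The point holds for one contrast in one sensitivity analysis. The planned rule is a proper adverse scenario for TG against CG and UG against CG, but not for TG against UG. At 20% missing per arm it leaves that contrast at −5.0 mmHg (arm-mean shift) or −4.0 (common value), where an adverse scenario gives −3.0 to +1.5 over D = 5 to 16.3. With 15% missing in TG and 25% in UG, the arm-mean version moves it to between −5.5 and −6.6, in TG's favour. These figures rest on the planning means and the assumed D and missing shares.

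The blinding matter is secondary. The passages need reconciling, but the analysis is not impossible. The primary intention-to-treat analysis and the sample size are unaffected.

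**What to change.** 1. In 2.7, add a run for TG against UG with missing TG values imputed as deteriorated and missing UG values as improved. Delta-adjusted imputation with a separate shift per arm, reported as a tipping point, is one way to do this.
2. State that the planned rule is a worst case for the two comparisons with control only, and do not describe it as one for TG against UG.
3. Reconcile 2.7 with 2.3.2 and 3.3. Either lock the primary model on coded arms and then release labels for the arm-directed sensitivity analyses, or run them under every possible labelling and select at unblinding. The second route takes three runs for the planned rule. For the added run it takes 3 × 2 = 6 ordered pairs of arms.

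The cost is a few sentences and modest programming, with no new data. The changes should be made before unblinding.

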## Research management

3

This study has been approved and is overseen by the Ethics Committee of the Pujiang County Traditional Chinese Medicine Hospital. A Data Monitoring Committee (DMC), consisting of two independent members with no conflicts of interest, will supervise the trial and conduct safety and progress assessments every 6 months. All research staff must complete standard operation procedure (SOP) and ethics training.

